## Abstract

**Background:**

In orthodontic treatment, anchorage control is a fundamental aspect. Usually conventional mechanism for orthodontic anchorage control can be either extraoral or intraoral that is headgear or intermaxillary elastics. Their use are combined with various side effects such as tipping of occlusal plane or undesirable movements of teeth. Especially in cases, where key-teeth are missing, conventional anchorage defined as tooth-borne anchorage will meet limitations. Therefore, the use of endosseous implants for anchorage purposes are increasingly used to achieve positional stability and maximum anchorage.

**Methods/Design:**

The intended study is designed as a prospective, multicenter randomized controlled trial (RCT), comparing and contrasting the effect of early loading of palatal implant therapy versus implant loading after 12 weeks post implantation using the new ortho-implant type II anchor system device (Orthosystem Straumann, Basel, Switzerland).

124 participants, mainly adult males or females, whose diagnoses require temporary stationary implant-based anchorage treatment will be randomized 1:1 to one of two treatment groups: group 1 will receive a loading of implant standard therapy after a healing period of 12 week (gold standard), whereas group 2 will receive an early loading of orthodontic implants within 1 week after implant insertion. Participants will be at least followed for 12 months after implant placement.

The primary endpoint is to investigate the behavior of early loaded palatal implants in order to find out if shorter healing periods might be justified to accelerate active orthodontic treatment. Secondary outcomes will focus e.g. on achievement of orthodontic treatment goals and quantity of direct implant-bone interface of removed bone specimens. As tertiary objective, a histologic and microtomography evaluation of all retrieved implants will be performed to obtain data on the performance of the SLA surface in human bone evaluation of all retrieved implants. Additionally, resonance frequency analysis (RFA, Osstell™ mentor) will be used at different times for clinically monitoring the implant stability and for histological comparison in order to measure the reliability of the resonance frequency measuring device.

**Trial registration:**

Current Controlled Trials ISRCTN97142521.

## Background

Control of anchorage for orthodontic tooth movements represents a fundamental problem in the treatment of dental and skeletal dysgnathia. Available anchorage potential [1,2], and that required for each anchoring task, must be taken into consideration if undesired tooth movements and anchorage loss are to be avoided. To avoid uncontrolled tooth movements, the existing anchorage potential of the natural teeth has to be balanced to the required anchorage task. This may pose a clinical challenge when strict positional stability and maximal anchorage is intended.

According to these general rules, a reduced number of anchor teeth, advanced loss of periodontal attachment or an unfavourable distribution of teeth represent the typical clinical findings to consider skeletal anchorage [3]. When traditional anchorage concepts like the Nance button appliance or a lingual arch or even extraoral (headgear or Delaire face mask) devices are applied in these demanding cases, they often produce unpredictable reactive forces and moments [4,5]. Specifically, they often lead to protrusion of the incisors, extrusion and tipping of the anchoring teeth, and interfere with the alignment of the occlusal plane.

For these reasons, temporary orthodontic anchorage implants were developed for the maxilla in the early 1990s. Usually, according to the present manufacturers' instructions and to conventional loading concepts in general dental implantology, palatal implants are loaded after a healing period of 3 (-4) months. Recently, improvements in general implant design and surface, which have increased bone-to-implant contact rates, have encouraged changes in conventional loading protocols in favour of early and immediate loading concepts [6-8].

According to experimental and clinical literature and to previous consensus statements [9,10], reduced implant healing times can be recommended in many implant indications. However, comparative clinical trials concerning immediate and early loading of palatal implants used for maximum anchorage are rare at present [11].

Therefore, this study will focus on early implant loading using the new ortho-implant type II anchoring device (Orthosystem^®^, Straumann, Basel, Switzerland) to investigate if shorter healing periods might be justified in order to accelerate orthodontic treatment.

## Methods/Design

### Study design

The study is designed as a prospective, multicenter randomized controlled clinical trial. The study was approved by the Ethics Committee of the State Medical Council of Rhineland-Palatinate, Germany (Ref. No: 837.210.06 (5308)).

A formal coordination center for clinical trials (KKS Mainz, Germany) will monitor study progress and assure data accuracy.

### Study objectives

The objective of the clinical study proposal will be to investigate the performance of early functional palatal implant loading in order to find out if:

- early orthodontic loading without the typical healing period is a clinically safe procedure

- and might, thus, be justified to accelerate active orthodontic treatment.

Therefore, the study will compare and contrast the efficacy and results of early functional implant loading within 1 week versus conventional implant loading after 12 weeks post implantation.

Concerning this matter the following null hypothesis will be addressed: There will be no difference between standard therapy and early loading group concerning implant failure rate.

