### Sample Size

For sample size calculation an implant failure rate of 5 % for group 1 (implant loading after a post-surgical healing period of 12 weeks) an implant failure rate of 25 % for group 2 (early implant loading within 1 week post implantation) was assumed. Based on 0.8 power to detect a significant difference at the two sided 5% level with an assumed loss to follow-up of 5 %, 62 patients in each group and 124 in total will be required. Sample size calculation, which based on clinical experiences with the new Orthosystem type II and early functional loading of conventional dental implants, was estimated with nQuery Advisor^® ^(Version 3.0) by the Institute of Medical Biostatistics, Epidemiology and Informatics (WH), University of Berlin, Germany.

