## Discussion

Clinical investigations and experimental studies indicate that endosseous implants e.g. palatal implants are resistant to orthodontic force application and can be used to achieve positional stability and therefore to enhance orthodontic anchorage [1,2,4,5,8,11]. Usually, according to the present manufacturers' instructions and to conventional loading concepts in general dental implantology, the healing period for palatal implants must not fall short of 3 to 4 months.

Recent findings from clinical and experimental studies suggested the possibility of loading palatal implants earlier than 12 weeks. Borbély and coworkers [8] showed, that an sufficient amount of osseointegration could be achieved at about 4 weeks after surgery or even at an earlier time. This result was based on clinical and histological evaluation in an experimental animal study (foxhounds). Study endpoints were defined as implant loss and implant stability after 1 and 6 months of loading.

Crismani and coworkers [11] initiated a clinical pilot study to evaluate the behaviour of 20 early loaded palatal implants over an observation time of 12 weeks. They reported a success rate of 90% for implants functionally loaded after a healing period of 1 week. The implants, however, were observed no longer than for the 12 week period.

Therefore, we initiated an RCT study comparing and contrasting the effect of early loading of palatal implant therapy versus implant loading after 12 weeks post implantation using the new ortho-implant type II anchor system device (Orthosystem Straumann, Basel, Switzerland). The results of this trial will be presented as soon as they become available.

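### The aim is to show early loading safe and justified, but the only stated test is of no difference, with no criterion for acceptable excess failure

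*Protocol article*

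**What the plan says.** The protocol article, under Study objectives, sets out to learn whether "early orthodontic loading without the typical healing period is a clinically safe procedure" and whether it "might, thus, be justified to accelerate active orthodontic treatment". It then gives one null hypothesis for this question: "There will be no difference between standard therapy and early loading group concerning implant failure rate".

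The Sample Size section assumes an "implant failure rate of 5 % for group 1" (loading after 12 weeks) and, for early loading, states that "an implant failure rate of 25 % for group 2 (early implant loading within 1 week post implantation) was assumed". The trial is sized on 0.8 "power to detect a significant difference" at the two-sided 5% level, with 5% loss to follow-up, giving 62 patients per group and 124 in total.

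The article states no non-inferiority or equivalence margin, no largest tolerable excess failure and no confidence-limit criterion. The only other numerical failure threshold is under Statistical analysis: early termination if more than 50% of implants fail in any group at the interim look. That is a stopping threshold, not a standard for calling early loading acceptable.

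**The concern.** The objective is a claim of acceptability: early loading does not cost too many implants, so the healing period can be shortened. The test is built for the opposite claim, that early loading is much worse. A significant result in the planned direction argues against early loading. A non-significant result leaves the question open unless the confidence interval is also judged against something.

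At stake is what the trial can conclude. Without a criterion for acceptable excess failure, the favourable conclusion could come only from a test that failed to reject. Such a test fails to reject more often when the trial is smaller or the data are noisier, so a weaker trial would make early loading look safer.

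**Working it through.** **Inputs.** Failure 5% (group 1) and 25% (group 2), two-sided alpha 0.05, power 0.80, loss 5%, 62 per group, all from Sample Size. 1:1 allocation, from Randomization.

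**1. The plan's own figure.** The mean of the two rates is 0.15.
- Uncorrected: n = [1.960·√(2·0.15·0.85) + 0.842·√(0.05·0.95 + 0.25·0.75)]² / 0.20² = (0.990 + 0.408)² / 0.04 = 48.8, so 49 per arm.
- Continuity-corrected: n = (48.84/4)·[1 + √(1 + 4/(48.84·0.20))]² = 58.4, so 59 per arm.
- With 5% loss: 59 × 1.05 = 61.95, so 62. The stated size is reproduced.
- Evaluable per arm: 62 × 0.95 = 58.9, about 59.

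The plan is therefore a continuity-corrected two-sided difference calculation. At 59 per arm the continuity-corrected chi-square test has the same power as Fisher's test for the rates below, so the Fisher column is closest to the plan's own basis.

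**2. Chance of a non-significant result.** Exact enumeration over two binomials, 59 per arm, true group 1 failure 5%:

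| True group 2 failure | Fisher | Uncorrected chi-square |
|---|---|---|
| 10% | 91% | 83% |
| 15% | 68% | 55% |
| 20% | 38% | 27% |
| 25% | 16% | 10% |

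**3. What a non-significant result can leave open.** Take 3/59 (5.1%) against 9/59 (15.3%), a difference of 10.2 points.
- Fisher p = 0.125; uncorrected chi-square p = 0.068.
- The Wilson limits are 1.7% to 13.9% for group 1 and 8.2% to 26.5% for group 2.
- Newcombe upper limit: 10.17 + √[(26.52 − 15.25)² + (5.08 − 1.74)²] = 10.17 + 11.75 = 21.9 points.
- Newcombe lower limit: 10.17 − √[(15.25 − 8.24)² + (13.92 − 5.08)²] = −1.1 points.

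So a result compatible with more than the 20-point excess used for planning would not reject the null. For 3/59 against 6/59 (Fisher p = 0.49) the upper limit is 15.9 points; for 3/59 against 3/59 it is 9.4 points.

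**4. Could a significant result favour early loading?** Not realistically at the planned control rate. With 3 failures in group 1, even 0/59 in group 2 gives a Fisher p of 2·(59·58·57)/(118·117·116) = 0.24. The uncorrected chi-square is (3/59)² / [(3/118)·(115/118)·(2/59)] = 3.08, p = 0.08. Non-rejection is the only realistic route to a favourable reading.

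**5. What 59 per arm could support.** Suppose both arms truly fail at 5% and the rule is that the upper Newcombe 95% limit lies below a margin. The documents give no margin, so those below are assumptions. Exact power is 59% for 10 points, 73% for 12, 78% for 13, 86% for 14 and 89% for 15. About 80% is reached at 13 to 14 points.

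For a 10-point margin at 80% power, the normal approximation gives n = (1.960 + 0.842)²·2·0.05·0.95/0.10² = 75 per arm, or 79 with loss (158 in total). That approximation is optimistic for the Newcombe rule: at 59 per arm it gives about 70% power, against the exact 59%.

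**The case against.** The null, the two-sided test and the sample size agree with one another. The planners feared that early loading would be worse and sized the trial to detect a large excess, which is a legitimate aim; at a true 25% the test finds it in 84% to 90% of trials. The objectives are worded as a question, not as a decision rule. The article is condensed, so rules for interpretation and interval reporting may be in documents not shown. All of this stands, and it places the fault in the link between objective and hypothesis rather than in the calculation. It does not remove the fault: the objective, the hypothesis and the basis for the size are all stated here, and a margin normally belongs to the design at that level.

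Three stronger readings are tempting but unsupported.
- A reader might infer that the investigators will declare safety from p > 0.05. The article never says so; it only ties the safety question to this null and offers no other criterion.
- A reader might take the Discussion's pilot ("They reported a success rate of 90% for implants functionally loaded after a healing period of 1 week") as fixing the true early-loading failure rate near 10%. It had 20 implants observed for 12 weeks, whereas the primary endpoint is at 6 and 12 months. Two failures in 20 has an exact 95% interval of about 1% to 32%, which includes the planned 25%.
- A reader might conclude that every non-significant result leaves a large excess open. That depends on the data: with 3 failures in group 1, the upper limit reaches 20 points only from about 8 or 9 failures in group 2.

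**Conclusion.** The concern holds as a mismatch between objective and test. The stated inference can show that early loading is considerably worse, but it contains no criterion by which early loading could be shown acceptable. A non-significant result alone would not support a conclusion of safety or justification: a tripling of failure from 5% to 15% would be missed in 55% to 68% of trials, depending on the test.

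These figures assume 59 evaluable patients per arm and a true 5% failure rate under standard loading. The article names no test, so both are shown. The point should be fixed, but it does not invalidate the design: the sample size is correctly calculated for the difference it targets, and the remedy is wording and a decision rule.

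**What to change.** Keep 124 patients and amend Study objectives and Statistical analysis as follows.

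- Base any safety conclusion on the upper limit of the two-sided 95% confidence interval (for example Newcombe) for the failure-rate difference, group 2 minus group 1. If the sponsor adopts and clinically justifies an acceptable excess, state it in advance and compare the limit with it.
- State that p > 0.05 is not evidence of safety.
- Disclose what the size supports: about 80% power only for a margin of about 13 to 14 points, and 59% for 10 points, if both arms truly fail at 5%. Whether any such margin is acceptable is for the sponsor to argue; a tighter one would need more patients or lower power.
- If no margin is adopted, restate the aim as detecting an excess of about 20 points, and draw no conclusion of safety or justification from a non-significant test.

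The cost is a change of wording in the protocol and any analysis plan, with no extra patients. The downside is a less favourable, explicit statement of how much excess failure the trial can exclude.

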### Patients

Males or females whose diagnoses require temporary stationary implant-based orthodontic anchorage treatment will be included in the study. Inclusion criteria for the study are as follows:

• Orthodontic indication for skeletal anchorage

• Adequate bone quantity for a palatal implant in the lateral cephalogram

• Good oral hygiene and normal wound healing capacity

• Written informed consent

Patients with cheilognathopalatoschisis and other syndromes associated with craniofacial anomalies are to be excluded. Other exclusion criteria are patients with immunodeficiency, diseases requiring a prolonged steroid usage, previous radiation therapy or chemotherapy, patients with metabolic bone diseases or uncontrolled endocrine disorders, alcohol or drug abuse as well as pregnancy.

### Study interventions

Implant loading after a post-surgical healing period of 12 weeks (standard therapy, group 1) versus early implant loading within 1 week post implantation (group 2).

### Study device

The new ortho-implant type II anchor system (Orthosystem^®^, Straumann, Basel, Switzerland; Fig.1) available with diameters of 4.1 mm and 4.8 mm, is a pure titanium 1-piece device. It consists of a endosseous implant body, a transmucosal implant neck, abutment, fixation cap and occlusal screw, all parts being made of pure titanium except the occlusal screw (stainless steal). The endosseous implant body has a self-tapping thread with a sandblasted, large grit, acid-etched (SLA^®^) surface. A set of burs and instruments is available for implant insertion and removal. For orthodontic treatment the implant will be connected to a rotationally secure steel abutment coping (length: 3.6 mm; diameter: 5.0 mm), onto which orthodontic arches are fixed in position by laser welding.

**Figure 1 F1:**
[figure not shown]
Schematic representation of an orthodontic anchorage implant (ortho-type II, Straumann, Basel, Switzerland). The Ortho-type II implant is available in the dimensions 4.1 mm (4.8 mm) × 4.2 mm.

### Implant Insertion

Cephalometric analysis of lateral radiographs must be available to determine the optimal implant insertion site. Implants will be inserted in the paramedian or median palatal area to obtain good primary stability and maximum bone integration of the implant surface.

Preoperative antibiotic prophylaxis will be given before implant's insertion. Surgical placement of the implant in the maxillary anterior area will be done under local anesthesia (palatine and incisal nerves) according to the manufacturers' instructions [12]. Oral hygienic instruction must be given by the surgeon comprising the use of chlorhexidine digluconate solution.

Lateral radiograph must be performed post surgery in order to verify the correct position and angulation of the implant.

### Sample Size

For sample size calculation an implant failure rate of 5 % for group 1 (implant loading after a post-surgical healing period of 12 weeks) an implant failure rate of 25 % for group 2 (early implant loading within 1 week post implantation) was assumed. Based on 0.8 power to detect a significant difference at the two sided 5% level with an assumed loss to follow-up of 5 %, 62 patients in each group and 124 in total will be required. Sample size calculation, which based on clinical experiences with the new Orthosystem type II and early functional loading of conventional dental implants, was estimated with nQuery Advisor^® ^(Version 3.0) by the Institute of Medical Biostatistics, Epidemiology and Informatics (WH), University of Berlin, Germany.

### Randomization

At each center, investigators and participants will be kept from knowing which patient will be assigned to which treatment group until post implant insertion. When according to the surgeon intraoperatively implant primary stability is given, participants will be randomly assigned either to the control or experimental group. Randomization will be performed in a 1:1 ratio using a balanced design with a block of 4 to treatment based on a computer-generated randomization code by an Institute of Medical Biostatistics (KKS, Mainz, Germany).

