### Outcome measurements

#### Primary Clinical Endpoints

Implants' stability after a loading time of 6 and 12 months of function after implant placement. The criteria of implant success are:

- implant survival

- no abnormal mobility

Implant stability will be tested post implant placement and throughout the orthodontic controls using the percussion test. Therefore the palatal implant in each case will be tapped then in vertical and horizontal directions using an instrument grip to test the subsequent resonance on percussion. High acustic sound response will indicate good primary and secondary implants' stability respectively, whereas dull acustic sounds will indicate loss of implants' stability.

In addition, resonance frequency analysis (RFA, Osstell™ mentor) will be used at time of surgery and at different times during postoperative checkups and finally after completion of active treatment. Resonance frequency analysis, firstly introduced by Meredith [13], is a method for clinically monitoring the implant stability in implant stability quotient (ISQ) units, which is scaled from 1 to 100. For measuring implant stability the orthodontic suprastructures will be removed.

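### A single published block size of 4, with visible arms and the surgeon's own stability judgement as the last gate, lets some upcoming allocations be anticipated

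*Protocol article*

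**What the plan says.** The Randomization section of the protocol article fixes the scheme: "Randomization will be performed in a 1:1 ratio using a balanced design with a block of 4". No other block size is mentioned. The code is computer-generated by an institute outside the centres.

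The same section places the entry decision just before allocation: "When according to the surgeon intraoperatively implant primary stability is given, participants will be randomly assigned". Investigators and participants "will be kept from knowing which patient will be assigned to which treatment group until post implant insertion".

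The arms, under Study interventions and again under Orthodontic treatment and superstructure, are loading within 1 week and loading after 12 weeks. Nobody treating the patient can miss which was assigned.

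Under Primary Clinical Endpoints, stability is tested by percussion and judged by sound: "High acustic sound response will indicate good primary and secondary implants' stability respectively". Resonance frequency analysis (RFA) is also done at surgery, but no RFA value is tied to entry. Success there means implant survival without abnormal mobility.

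The Study design section calls the trial multicentre. The article states neither the number of centres nor whether blocks run within centre.

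**The concern.** Withholding the current assignment until after insertion protects it only if it cannot be worked out from earlier ones. With one known block size and visible arms, part of the sequence can be. The step just before release is a personal judgement that decides whether the patient enters the trial.

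A surgeon who expects early loading next may be stricter with a borderline implant, and more lenient when expecting 12 weeks of healing. That would place firmer implants in group 2 and shrink the observed difference. The gate and the primary endpoint concern the same attribute, implant stability. Expected failures are few: on the Sample Size assumptions, 0.05 × 62 ≈ 3 in group 1 and 0.25 × 62 ≈ 15 in group 2. A handful of selectively excluded implants could therefore matter.

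**Working it through.** **Inputs.** Block size 4 and ratio 1:1 (Randomization); 62 per group, 124 in total, failure rates 5% and 25%, power 0.8, two-sided 5%, 5% loss (Sample Size). 124 / 4 = 31 full blocks.

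**The plan's own figure.** The article gives no predictability figure. Its sample size reproduces:

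- Mean failure rate (0.05 + 0.25)/2 = 0.15.
- n = [1.96√(2 × 0.15 × 0.85) + 0.842√(0.05 × 0.95 + 0.25 × 0.75)]² / 0.20² = 48.8 per arm.
- With continuity correction, (48.8/4) × [1 + √(1 + 4/(48.8 × 0.20))]² = 58.4, so 59.
- 59 × 1.05 = 61.95, so 62. (59/0.95 = 62.1 would give 63.)

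Nothing below changes this number.

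**Step 1: the guesser sees the whole block (blocking within centre).** The six possible blocks are AABB, ABAB, ABBA, BAAB, BABA and BBAA, which gives 24 positions.

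- Certain positions: the 4th in all six blocks (6), and the 3rd in AABB and BBAA (2). 8/24 = 33.3%, or about 124/3 ≈ 41 patients.
- Best guess by position: 1/2; 2/3; (1/3 × 1 + 2/3 × 1/2) = 2/3; 1. The mean is 17/24 = 70.8%, against 50% under simple randomisation.

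**Step 2: one list across k equal centres.** Assumptions: patients arrive in random order across centres; the surgeon knows the list position but sees only local allocations. Knowing the position favours the guesser. Let q = 1/k be the chance that an earlier allocation in the block was local.

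- Position 3 is certain if both earlier allocations are seen and are equal: q²/3.
- Position 4 is certain if both members of the arm already used up are seen: q².
- Average over four positions: (q²/3 + q²)/4 = 1/(3k²).
- Best guess by position: 1/2; 1/2 + q/6; 2/3 − (1 − q)²/6; 2/3 + q³/3 − (1 − q)³/6.

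| Centres sharing one list | Certain | Best guess |
|---|---|---|
| 1 (or blocks within centre) | 33.3% | 70.8% |
| 2 | 8.3% | 59.9% |
| 3 | 3.7% | 56.9% |
| 4 | 2.1% | 55.4% |
| 5 | 1.3% | 54.4% |

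Check for k = 2: (0.5 + 0.5833 + 0.625 + 0.6875)/4 = 0.599.

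**Step 3: effect of other block sizes, whole list visible.** Fixed sizes were enumerated. Mixed sizes were simulated (400 lists of 124), with a guesser who knows the set of sizes and updates optimally. Run with size 4 alone, the simulation returned 33.4% and 70.8%, in line with Step 1.

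| Scheme | Certain | Best guess |
|---|---|---|
| Fixed 4 | 33.3% | 70.8% |
| Fixed 6 | 25.0% | 68.3% |
| Fixed 8 | 20.0% | 66.6% |
| Random 4 or 6 | 5.6% | 69.2% |
| Random 4, 6 or 8 | 2.0% | 68.0% |

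Varying the size removes most of the certainty, but on its own it barely lowers the best-guess rate when the sizes are known.

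**The case against.** The strongest reply is that the size depends on something the article does not give. The phrase about each centre governs concealment, not blocking, and the code comes from one institute. With one shared list the certain share could be near 1%. This stands, and it is why a range is reported. Whether blocks run within centre is a detail an article may leave to the full protocol, so its absence is not criticised. The single block size, however, is stated and public.

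The route is also narrow. The implant is already placed when the gate applies, so selection on stability works only by declaring a placed implant not stable. How many implants are borderline is unknown. What is quantified here is guessability, not bias in the failure rates.

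Three stronger readings are tempting, and the article does not support them.

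- **That the next allocations can simply be deduced.** Even within centre, the first two positions of a block are never certain and the third is certain in only one block in three. Two thirds of allocations are not certain in advance.
- **That primary stability is the main determinant of failure under early loading.** The article says only that group 2 treatment starts when primary stability is good. It does not rank causes.
- **That no analysis could help.** RFA at surgery gives an instrumented baseline value that can be compared between arms and adjusted for. It may not remove all of the bias, but it is not nothing.

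Finally, judging stability before allocation is already the planned order. Only locking the verdict would be new.

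**Conclusion.** The point holds as an avoidable weakness of a stated design choice. Some allocations can be anticipated at the moment a borderline implant is judged stable or not: 33% with certainty and 71% by best guess if blocks run within centre, and about 8% to 1% with certainty if two to five equal centres share one list. These figures assume that the guesser knows the block size and remembers the allocations he or she can see; the shared-list figures also assume equal centres, random arrival and a known list position. The article shows a risk to the comparison of implant stability and survival. It does not show that selection has occurred or how large its effect would be. The change is worth making because it is cheap, but the weakness does not by itself invalidate the trial.

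**What to change.** For patients not yet randomised:

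1. Have the same institute regenerate the list with randomly varying block sizes, for example 4, 6 and 8, and do not disclose the sizes to the centres or in public documents.
2. Require the surgeon's stability verdict, together with the RFA value taken at surgery, to be registered irrevocably before the allocation is released. This makes the gate auditable and fixes the baseline value for later comparison of the arms.

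Both parts are needed. With the whole list visible, varying the sizes cuts certain allocations from 33% to about 2%, but the best-guess rate falls only from 71% to about 68% if the sizes are known.

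The cost is a new list, a short protocol change and one registration step. The downside is a slightly larger possible imbalance, at most half of the largest block per list: 8/2 = 4 patients instead of 4/2 = 2. The sample size stays at 62 per group.
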